### Interim analysis

An interim analysis will be conducted. We will use the Peto approach (i.e., *P* < 0.001) as the stopping rule for the primary efficacy endpoint (i.e., better outcomes for the RE group). The trial will not be stopped for futility (i.e., lack of differences between the VATE and RE groups) because the robot-assisted minimally invasive approach is increasingly being used by a number of different surgical centers worldwide and all of the endpoints of this randomized trial are expected to be of interest to healthcare professionals involved in this surgical procedure. As advised by the Central Committee on Research involving Human Subjects, no formal stopping rule for harm will be adopted. Upon recruitment of 50 patients, individualized patient description charts (including safety parameters) will be presented to the Data Safety Monitoring Committee (DSMC). The procedure will be repeated every 50 patients. Cases will be discussed by the DSMC in a plenary or telephone conference in the presence of the study coordinator and the PI. In the case of worse outcomes occurring in the RE group, the DSMC will inform the trial research group. The potential harm to each patient will be discussed by the DSMC and the trial research group in a plenary session aimed at determining whether an association exists between the observed adverse events and the use of RE. When a consensus will be reached, the Institutional Review Board will be informed accordingly.

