### Secondary endpoints

Secondary endpoints will include: the number of nodes removed along the right and left RLN; the incidence of pneumonia, defined according to the Revised Uniform Pneumonia Score which includes temperature, leukocyte count, and pulmonary radiography (Table 2) [25]; the incidence of other postoperative complications (e.g., anastomotic leakage, chylothorax), defined according to the Esophagectomy Complications Consensus Group system; the total percentage of surgery-related major postoperative complications (i.e., grade IIIa or higher according to the Clavien–Dindo criteria) [26]; in-hospital, 30-day, and 90-day mortality rates, defined as any death occurring during the same hospitalization and within 30 or 90 days after surgery, respectively; R0 resection rates, defined as microscopically negative proximal/distal and circumferential margins; surgery-related parameters (including thoracic, abdominal, and total surgical time (expressed in minutes); unexpected events and complications occurring during surgery (e.g., massive hemorrhage, perforation of other organs); blood loss during surgery (expressed in milliliters per phase); and number of patients requiring conversion to thoracotomy and related reasons); postoperative recovery parameters (including length of mechanical ventilator use after surgery (expressed in minutes), length of ICU stay (expressed in hours), length of hospital stay (expressed in days), and need for reintubation or readmission to the ICU); quality of life and psychometric measures (including the EORTC QLQ-C30, OES-18, and Hospital Anxiety and Depression Scale (HADS) questionnaires, administered at the following time points: 5 days before surgery; 4 weeks, 3 months, and 6 months after surgery; and on a yearly basis up to 5 years thereafter); and oncological outcomes (including 2-year, 3-year, and 5-year disease-free and overall survival rates).

**Table 2 Tab2:** Revised Uniform Pneumonia Score

Diagnostic criterion	Revised Uniform Pneumonia Score	
	Range	Score
Temperature (°C)	≥ 36.1 and ≤ 38.4	0
	≤ 36.0 and ≥ 38.5	1
Leukocyte count (× 10^9^/L)	≥ 4.0 and ≤ 11.0	0
	< 4.0 or > 11.0	1
Pulmonary radiography	No infiltrate	0
	Diffused (or patchy) infiltrate	1
	Well-circumscribed infiltrate	2

A sum score of 2 points or higher, in which at least 1 point is assigned because of infiltrative findings on pulmonary radiography, indicates the presence of pneumonia

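### Harm review rests on individual patient charts and per-patient attribution, names no comparison of event rates by arm, and states no response if outcomes are worse under VATE

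*Protocol article*

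**What the plan says.** All of the harm procedure is in the Interim analysis section of the protocol article.

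- **Formal rule.** There is none: "As advised by the Central Committee on Research involving Human Subjects", "no formal stopping rule for harm will be adopted".
- **Timing.** The first review comes "Upon recruitment of 50 patients", and then "The procedure will be repeated every 50 patients".
- **Material.** At each review, "individualized patient description charts (including safety parameters) will be presented to the Data Safety Monitoring Committee (DSMC").
- **Prompt.** "In the case of worse outcomes occurring in the RE group, the DSMC will inform the trial research group". No endpoint, measure or comparison is attached to it.
- **Next step.** "The potential harm to each patient will be discussed by the DSMC and the trial research group in a plenary session". The purpose is to decide whether the adverse events are associated with RE. The IRB is informed once consensus is reached.
- **VATE.** No response to worse outcomes in that arm is stated.

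The one numerical boundary in the section is P < 0.001 on the primary endpoint, for benefit of RE only.

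**The concern.** Under Surgical approach, both arms undergo the same two-field lymphadenectomy as part of an esophagectomy. Under Secondary endpoints, pneumonia, anastomotic leakage, chylothorax, major complications and death are counted in both arms. These events are expected at some background rate whichever technique is used. A chart showing a leak after RE seldom tells the reader whether the leak would also have occurred after VATE. Evidence that a technique raises the risk lies in the difference between the arms' rates, and the described steps do not mention it.

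The efficacy boundary does not cover this. It looks only for RE benefit, and its endpoint (no nodes retrieved, or permanent left RLN palsy) does not count death, leakage or pneumonia.

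At stake is whether a moderate excess of serious complications in one arm, spread over many individually plausible cases, would be recognised during a recruitment period of about three years. For VATE, the text gives the DSMC nothing to do even if it noticed one.

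**Working it through.** **1. The review schedule.** The Sample size section gives 95 per arm and 10% dropout: 95 / (1 − 0.10) = 105.6, rounded up to 106 per arm, or 212 in total. This matches the stated figure. Reviews every 50 patients fall at 50, 100, 150 and 200, so there are four, and the last 12 patients come after the fourth. With a 3-year inclusion period, accrual is 212 / 36 = 5.9 patients per month, and reviews are 50 / 5.9 ≈ 8.5 months apart.

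**2. What an excess looks like chart by chart.** Each review adds about 25 patients per arm. The article gives no complication or death rates, so the rates here and below are assumptions.

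| Assumed rates | Extra events per review |
|---|---|
| complications 20% vs 30% | 25 × 0.10 = 2.5 |
| complications 30% vs 45% | 25 × 0.15 = 3.75 |
| deaths 3% vs 6% | 25 × 0.03 = 0.75 |

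Two to four additional cases of a familiar complication are hard to recognise from charts read one at a time.

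**3. What a cumulative comparison by arm would show.** As a yardstick, take n = 25, 50, 75 and 100 per arm at the four reviews. With t events in total and x in the arm under suspicion, the one-sided Fisher P is Pr(X ≥ x), where X is hypergeometric (2n patients, t events, n in that arm). Flag if P < 0.05 at any review. At least 8,000 trials were simulated per scenario, assuming that outcomes are known at each review.

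| Assumed rates | Flagged by 200 patients |
|---|---|
| 20% vs 30% | 52% |
| 20% vs 40% | 93% |
| 30% vs 40% | about 47% |
| 30% vs 45% | 72% (43% by 100 patients) |
| 30% vs 50% | 90% |
| 3% vs 6% | about 18% |
| 3% vs 9% | 49% |
| 3% vs 10% | 59% |
| 30% in both arms | 7.9% (false) |
| 3% in both arms | 2.0% (false) |

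**4. False flags over both outcomes and both directions.** Simultaneous flags in opposite directions are rare, so each outcome contributes about twice its one-sided figure: 2 × 0.079 = 0.158 for complications and 2 × 0.020 = 0.040 for deaths. If the outcomes are treated as independent, 1 − (1 − 0.158)(1 − 0.040) = 1 − 0.842 × 0.960 = 0.19.

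**5. Data maturity.** Reviews are tied to recruitment. If surgery follows about 3 weeks after enrolment (assumed), 90-day status needs 21 + 90 = 111 days, or about 3.65 months. In that time 3.65 × 5.9 ≈ 21.5 patients are recruited, so only about 28 of the first 50 have 90-day data at the first review. The percentages in step 3 are therefore optimistic for 90-day deaths at the early reviews.

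**The case against.** The best defence has four parts.

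**A trigger exists.** A reader might infer that harm monitoring has no trigger at all. The text does not support that: worse outcomes under RE oblige the DSMC to inform the research group, and a plenary discussion and IRB notification follow. The wording is also comparative, so it implies some look at one arm against the other. This stands. What is missing is a definition of the prompt and any counterpart for VATE.

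**Nothing says that comparisons are withheld.** A reader might infer that an excess would pass all four reviews unnoticed. That is conjecture. The article does not say that the DSMC lacks arm labels or tabulations, and a charter or the full protocol, neither of which is shown, may provide them. This also stands, and it limits the point to the procedure as written. It does not remove the point, because the article sets the procedure out step by step and makes the individual patient the unit of attribution.

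**The absence of a formal rule is a declared choice.** It follows advice from a research ethics body, and DSMC judgement without a numerical boundary is a recognised option. This is correct, and the absence of a stopping rule is not the point here. A descriptive table by arm is compatible with that advice.

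**There is a second layer of review.** Under Quality control, a local committee regularly reviews outcome events and surgical videos, and disagreements go to a senior member of an international robotic surgery association. That has some value. But the local committee's members are involved in the conduct of the trial, and no comparison by arm is described for it.

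A nominal P < 0.05 flag is open to challenge too: it would usually miss a doubling of a low death rate, and it fires falsely in about one null trial in five. It serves above only as a yardstick.

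**Conclusion.** The point holds in a limited form. The stated harm review relies on individual charts and per-patient attribution. Its prompt is undefined and covers RE only, and no comparison of rates by arm is named. The gap is complete only for VATE, where no response is stated. For RE there is a qualitative prompt without content. This is a weakly fixed procedure. It is not a contradiction in the plan, and it does not show that harm would go undetected.

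The size depends on assumed rates. With complications near 30%, a cumulative comparison by arm would flag a 15-point excess in about 72% of trials and a 10-point excess in about 47%. It would flag a rise in deaths from 3% to 6% in only about 18%. The benefit is thus real for moderate or large excesses of common complications and small for rare events, for which case narratives remain important.

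**What to change.** Keep the DSMC, the 50-patient reviews and the advice against a formal stopping rule. Make three changes to the monitoring text:

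1. At each review, add to the charts a cumulative table by arm of all randomized and operated patients. It should give deaths at 30 and 90 days (each among patients who have reached that follow-up, with the denominator shown), complications of Clavien–Dindo grade IIIa or higher, and RLN palsy, with risk differences and confidence intervals.
2. Base the judgement on association with technique on that table, with case narratives as support.
3. Apply the procedure to both arms, so that worse outcomes under VATE also have a stated response.

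Any flag threshold, and any action that follows, should be left to the DSMC.

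**Cost.** A few sentences and one extra table per review, built from outcomes already collected under Secondary endpoints and Follow-up schedule. No new committee, visit or procedure is needed. The downside is that some chance imbalances will have to be discussed. If the DSMC chose a nominal one-sided 0.05 flag on deaths and major complications in both directions, about 19% of trials with equal arms would raise at least one false flag under the assumed 30% and 3% rates.

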## Discussion

The key prerequisite for reducing the burden of RLN palsy following RLN LND is a reliable identification of the anatomical course of the left RLN—which is unfortunately difficult to achieve. Blunt dissection and removal of lymph nodes located around the RLN may cause nerve contusions and heat injuries that can in turn result in postoperative palsy. In this scenario, RE holds great promise for reducing the likelihood of RLN damage owing to its inherent advantages, including the possibility to obtain a precise hemostasis and the capacity of performing multiaxial movements in a tension-free manner. Interest in RE is mounting, but only a paucity of studies have directly compared its results with those of VATE. Moreover, published studies have been limited by their retrospective design and lack of randomization. Importantly, the use of RE has been restricted to patients who expressed their willingness to undergo a partially insured robot-assisted operation (potentially introducing a selection bias related to the high socioeconomic status of patients for whom RE was affordable). A randomized allocation to either RE or VATE (as proposed in our current protocol) is expected to minimize the confounding impact of this variable. To our knowledge, there are no randomized trials of RE versus VATE, although a published randomized study has compared RE with open thoracotomy [27]. We believe that the REVATE study (Fig. 3) provides an opportunity to explore whether RE could facilitate LND along the left RLN—a complex surgical procedure that, as of now and with the use of VATE, remains difficult to perform and associated with a significant burden of morbidity in ESCC patients. If positive, our results will pave the way for a more widespread use of RE in ESCC, as well as for further cost-effectiveness comparative analyses of the two techniques.

**Fig. 3 Fig3:**
[figure not shown]
Robotic-assisted Esophagectomy vs Video-Assisted Thoracoscopic Esophagectomy (REVATE) trial logo

## Trial status

Ethics approval was granted from each participating institution before starting enrollment and consent will be obtained for each patient following local regulations. The protocol (20,180,828 version 2) has been prepared and reported in accordance with the Standard Protocol Items: Recommendations for Interventional Trials. The study was initiated on November 12, 2018 as originally planned, with a projected 3-year inclusion period. Analysis of short-term results and long-term oncological outcomes will begin at 6 months and 5 years after discharge of the last randomized patient, respectively.

## Data Availability

Raw data will be available from the corresponding author upon reasonable request. Transfers of clinical data will require approval from the Institutional Review Board.

## Abbreviations

CRF: Case record form
ESCC: Esophageal squamous cell carcinoma
GCP: Good clinical practice
HADS: Hospital Anxiety and Depression Scale
LND: Lymph node dissection
MIE: Minimal invasive esophagectomy
nCRT: Neoadjuvant chemoradiotherapy
RE: Robot-assisted esophagectomy
RLN: Recurrent laryngeal nerve
VATE: Video-assisted thoracoscopic esophagectomy
